### Follow-up

At the *Baseline *visit, demographics, earlier and ongoing disease, and concomitant medication are recorded. The baseline data include weight, height, and smoking and employment status. The patient completes a questionnaire that includes demographic data, the CTS symptoms severity scale, the 11-item disabilities of the arm, shoulder and hand (*Quick*DASH) questionnaire, and the SF-6D. A physical examination is performed.

At *5 weeks *after injection a telephone interview is conducted by the investigator and the patient is asked to complete the CTS symptoms severity scale and concomitant medication and adverse events (AEs) will be recorded.

At *10 weeks *after injection the patient is examined by the physical therapist. The investigator asks the patient whether she/he wants to proceed with surgery as planned at 12 weeks after injection or whether the patient has experienced adequate symptom relief that she/he wants to continue follow-up and not have the planned surgery at this stage. An evaluation similar to the baseline evaluation is performed and the indication for surgery is recorded. The patient completes the CTS symptoms severity scale. Concomitant medication and AEs are recorded. Possible use of a wrist splint since the injection and its frequency is recorded.

At 12 weeks the patient who had chosen to have surgery is operated on as scheduled.

At *24 weeks *after injection the patient is examined and asked to complete a questionnaire including the CTS symptoms severity scale, *Quick*DASH, and the SF-6D as well as to rate satisfaction with the treatment on a visual analog scale from 0 (very dissatisfied) to 100 (completely satisfied). Concomitant medication and AEs are recorded.

At *52 weeks *after injection the patient is asked to attend a physical examination and nerve conduction tests and complete the questionnaires.

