### Primary endpoint

1. The CTS symptom severity score change at 10 weeks after treatment:

1) 80 mg Methylprednisolone vs. placebo

2) 40 mg Methylprednisolone vs. placebo

3) 80 mg Methylprednisolone vs. 40 mg Methylprednisolone

2. The rate of surgery at (in rank order) 52 weeks, 24 weeks, and 12 weeks after treatment:

1) 80 mg Methylprednisolone vs. placebo

2) 40 mg Methylprednisolone vs. placebo

3) 80 mg Methylprednisolone vs. 40 mg Methylprednisolone

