### Secondary endpoint

1. The CTS symptom severity score change at 52 weeks

2. Time to surgery

3. The *Quick*DASH score at 10 weeks and 52 weeks

4. The SF-6D score at 10 weeks and 52 weeks

5. Patient satisfaction with treatment at 10 weeks and 52 weeks

6. Duration of sick leave at 52 weeks (for employed patients)

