### Statistical Analysis

All patients who have been randomized and have received an injection will be included in the statistical evaluation. Statistical tests will be performed and reported according to the intention-to-treat principle. Data will be presented as mean and standard deviation or median and range, as appropriate, for continuous variables and as numbers and proportions for categorical variables. The primary analysis of the CTS symptom severity score at 10 weeks will be performed using a mixed model analysis of repeated measures (baseline, 5 weeks, 10 weeks) with treatment effect (placebo or Methylprednisolone) and time as fixed factors in a first step and with the interaction term of treatment and time in second step. The results will be presented as differences in mean score change over time (baseline to 10 weeks) and 95% confidence intervals. The secondary analysis of the symptom severity score will be done using a mixed model with treatment (placebo or Methylprednisolone) as a random factor and time (baseline, 5 weeks, 10 weeks, 24 weeks, 52 weeks) as fixed factor and surgery as covariate; first step without interaction terms and second step with two-way interaction of treatment and time. The results will be presented as differences in mean score change over time and 95% confidence intervals.

The primary analysis of rate of surgery will be done using Fisher's exact test (univariate) and logistic regression (multivariate) with adjustment for baseline variables. The issue of multiplicity is addressed by performing the analysis in the following priority; 52 weeks, 24 weeks, and 12 weeks. The results will be presented as differences in the rate of surgery between the groups (Methylprednisolone compared with placebo) and as adjusted odds ratio (and 95% confidence interval) of having surgery at each time point. The possible dose-response relationship with higher effect of high dose will be explored by prioritizing group comparisons. We will conduct the following predefined subgroup analyses; symptom duration (12 months or shorter versus more than 12 months), symptom severity (baseline symptom severity score below 3.0 versus 3.0 or higher), and median nerve conduction abnormality (moderate or severe versus mild or normal).

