Analysis of the secondary end-points will be done with mixed models adjusting for baseline variables. We will also calculate the effect size for the symptom and function scales [20]. The AEs will be reported in table form and stratified in 4 groups according to severity; statistical comparison will be done when appropriate. When at least 60 patients have completed the 24-week visit the frequency of SAEs and of AEs with persistent symptoms will be calculated and the results will be reported and discussed with the Swedish Medical Products Agency.

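### Mixed models are assigned to every secondary endpoint, but time to surgery is a single, right-censored value per patient and needs a time-to-event method

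*Protocol article*

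**What the plan says.** The Secondary endpoint section lists six endpoints. Four are questionnaire scores or ratings: symptom severity, QuickDASH, SF-6D and satisfaction. The other two are "Time to surgery" and "Duration of sick leave at 52 weeks (for employed patients").

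The Statistical Analysis section gives one method for the group: "Analysis of the secondary end-points will be done with mixed models adjusting for baseline variables". Two other methods are tied to specific endpoints. For the surgery rate at fixed times: "The primary analysis of rate of surgery will be done using Fisher's exact test (univariate) and logistic regression (multivariate"). For the symptom score over all visits: "The secondary analysis of the symptom severity score will be done using a mixed model with treatment" and further terms. No survival method is named anywhere in the article. The same section includes every patient who was randomized and injected, under intention to treat.

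The Follow-up section shows how the surgery times arise. At week 10 the patient chooses. For those who want the operation, "At 12 weeks the patient who had chosen to have surgery is operated on as scheduled". A patient with enough relief may say that "she/he wants to continue follow-up and not have the planned surgery at this stage". Operations after week 12 are expected, because the primary endpoint is "The rate of surgery at (in rank order) 52 weeks, 24 weeks, and 12 weeks after treatment".

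**The concern.** A mixed model of the usual kind describes repeated measurements on the same patient, each of them observed. Time to surgery fails on both counts. A patient has at most one surgery time, so there is no repetition to model. A patient who has not been operated on by week 52, or who is lost before then, has only a lower bound.

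This is not a detail left to a fuller document. The article names a method, and that method does not fit one of the endpoints it covers. An analyst who follows it must settle, perhaps after seeing data, how unoperated patients enter the model. That choice can drive the estimate, because avoiding or delaying surgery is what this endpoint is meant to measure.

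**Working it through.** **The plan's own figures.** The plan gives no figure for time to surgery. Its sample size is relevant only for the loss it allows. For 0.8 points, SD 1.0, 90% power and two-sided 5%, the normal formula gives 2 x (1.960 + 1.282)^2 / 0.8^2 = 32.8, so 33 per arm. With the noncentral t distribution 33 per arm gives 89.3% power and 34 gives 90.2%, so 34 x 3 = 102 reproduces. Enrolling 120 to retain 102 allows for 1 - 102/120 = 15% incomplete follow-up.

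**One value per patient.** A random-intercept model was fitted to 80 simulated patients, 40 per arm, with one value each. The intercept variance cannot be separated from the residual variance: the Hessian was not positive definite and the total variance of 0.919 was split arbitrarily into 0.459 and 0.459. The standard error reported for the treatment difference was 0.152, which is sqrt(2 x 0.459/40). The total variance gives sqrt(2 x 0.919/40) = 0.214, the ordinary least-squares value. The random part adds nothing here and, in this software, spoiled the standard error.

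**Censoring.** The illustration uses assumed rates. A share p12 is operated on at week 12, further operations up to a total share p52 are spread evenly over weeks 13 to 52 (mean 32.5), and the rest are unoperated at week 52.

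- Unoperated left out: mean = [12 x p12 + 32.5 x (p52 - p12)] / p52
- Unoperated set to 52: mean = 12 x p12 + 32.5 x (p52 - p12) + 52 x (1 - p52)

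For 60%/90% on placebo and 50%/60% on active (weeks 12/52):

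- Left out: placebo (7.2 + 9.75)/0.9 = 18.8; active (6.0 + 3.25)/0.6 = 15.4; difference -3.4 weeks. Active looks faster to surgery although fewer patients have it.
- Set to 52: placebo 16.95 + 5.2 = 22.15; active 9.25 + 20.8 = 30.05; difference +7.9 weeks.

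The same formulas give the other rows. Rejection rates at 5% come from 4000 simulated trials with 40 patients per arm and no loss to follow-up, using a t-test for the two means.

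| Placebo vs active, weeks 12/52 | Left out: difference (rejects) | Set to 52: difference (rejects) | Log-rank rejects |
|---|---|---|---|
| 60/90 vs 50/60 | -3.4 (21%) | +7.9 (53%) | 82% |
| 60/90 vs 40/75 | +2.7 (15%) | +7.0 (47%) | 51% |
| 50/80 vs 25/60 | +4.3 (25%) | +9.0 (64%) | 60% |

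With equal arms (60/90 in both) all three reject in about 5% of runs.

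**Incomplete follow-up.** Take a patient last seen unoperated at week 24. The true time, cut at 52, lies somewhere from 24 to 52, so an assigned value can be wrong by up to 28 weeks. If the full 15% allowance were lost in this way, one arm's mean could shift by up to 0.15 x 28 = 4.2 weeks. The shift cancels between arms only as far as loss and later surgery are alike in them. A censored analysis needs no assigned value.

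**The case against.** Five arguments have weight.

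1. The sentence is a summary in a journal article. Effect sizes for the symptom and function scales follow directly, so the authors may have had only the scores in mind. That is plausible, but the sentence carries no limit and no other method is offered for time to surgery. The phrase mixed models also does not say linear, but no grouping is described that would call for a mixed survival model.

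2. Leaving out unoperated patients would break the section's own analysis set. This stands, and it makes the left-out column an analysis that the plan rules out. What remains is to assign a time, and no rule for that is stated.

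3. A reader might infer that entering 52 weeks always understates the effect. It does not. With complete follow-up this is a comparison of restricted mean time to surgery, a legitimate quantity. In the simulation it was clearly weaker than log-rank in one scenario, close in another and slightly stronger in the third. The weakness is the missing rule and the expected loss to follow-up.

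4. A reader might infer that operated patients all have times near 12 weeks, so that no difference could show. The documents do not support this: surgery is declined only for the time being and is counted again at 24 and 52 weeks. The differences among operated patients above are not zero. Nor do ties at week 12 invalidate a mixed model; they matter only for the replacement.

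5. A reader might extend the same verdict to sick leave. The endpoint is one 52-week total per employed patient, but Table 2 schedules reports at five visits and the documents state no share of zeros. The Background gives a median absence of 4 weeks after surgery with some long-term disability. That makes skewness likely, but it concerns other studies. The mixed model is ill-suited there, not strictly invalid.

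**Conclusion.** The point holds for time to surgery: the assigned method does not fit the endpoint, because there is one value per patient and no means of handling censoring. The firm part rests on the text alone. The sizes rest on assumed surgery rates: under them the estimate moves between -3.4 and +7.9 weeks in one scenario according to how unoperated patients are entered, and the loss the plan allows for could shift one arm's mean by up to 4.2 weeks.

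The reach is limited to one secondary endpoint. A reader might conclude that the trial's finding on surgery is at risk. It is not: the surgery rate at 52, 24 and 12 weeks is a primary endpoint with its own binary analysis, in which unoperated patients are counted. Sick leave is a minor point of suitability.

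**What to change.** - Limit the mixed-model sentence to the repeatedly measured scales: symptom severity, QuickDASH, SF-6D and satisfaction.
- For time to surgery, specify Kaplan-Meier curves and a log-rank test, plus Cox regression with a named method for ties. A discrete-time model is an alternative, since planned operations cluster at week 12. Censor unoperated patients at 52 weeks or at last contact if earlier.
- If a restricted mean is preferred as a summary, say so and estimate it from the Kaplan-Meier curve, so that early loss is handled.
- Optionally, compare the 52-week sick-leave total with a rank-based test or a bootstrap interval.

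The sample size does not change. The cost is analysis wording, on one condition: Table 2 lists the rate of surgery at 12, 24 and 52 weeks but names no surgery date, so confirm that the date, or at least the visit interval, is recorded. If only the interval is known, use the discrete-time model.

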## Discussion

In this double-blind placebo-controlled randomized trial of patients with moderately severe idiopathic CTS we intend to investigate the medium-term efficacy of steroid injection into the carpal tunnel and the possible presence of a dose-response relationship first at 10 weeks but also at 24 weeks and 52 weeks. The strength of this trial is that it will be performed at one orthopedic department to which the vast majority of patients with CTS from the study region are referred. In addition, steroid injection is rarely used as a treatment for primary idiopathic CTS by primary care physicians who usually treat patients with CTS in the study region before referring them to the orthopedic department.

A potential factor that may influence the results is that all patients are given the choice to have surgery at 12 weeks if their symptoms have not improved adequately. Before inclusion in the trial all the patients have unsuccessfully undergone treatment with wrist splinting and have symptoms of such severity that warranted referral to the orthopedic department. Because surgery is the only remaining treatment option with a strong evidence of efficacy there is no ethically acceptable alternative to offering surgery after 12 weeks. This trial will not answer the question of whether steroid injection is effective in patients with CTS that failed wrist splinting but the severity of which is judged by the patient as mild and not warranting surgery or in patients declining surgery for other reasons. The use of the standardized CTS symptom severity scale in the trial will show the severity spectrum of CTS in the study population. Another factor is the potential multiplicity of the analyses but this is addressed by providing a rank order with which the analyses will be carried out.

Our goal is to determine the efficacy of two different doses of local steroid injection in the treatment of moderately severe CTS, taking into account the natural course of CTS and the placebo effect of injection. During the first 24 weeks the safety of steroid injection in the carpal tunnel will also be evaluated in comparison with placebo. The results will also be useful to predict the effect of treatment with steroid injection related to severity of CTS. Information on possible relationship between dosage and duration of effect also will be provided by this study.

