## Background

Carpal tunnel syndrome (CTS) is the most common peripheral compression neuropathy in the upper extremity with a prevalence of 3.7% in the adult general population [1]. The prevalence of persons who have moderate or severe CTS but have not sought care or been diagnosed correctly is almost 1% in the general population [2]. CTS of mild severity is commonly treated with wrist splint but for moderately severe symptoms surgical treatment is often required [3]. Carpal tunnel release is one of the most common surgical procedures; the annual incidence in a US population (2001-2005) was 134 per 100,000 [4]

Although carpal tunnel release has been shown to produce good outcomes regarding relief of symptoms caused by CTS [5], it has several disadvantages including surgery-related pain and hand weakness [6]. These are common problems and may last several months after surgery. Other less common complications include wound infection, chronic regional pain syndrome, and nerve injuries [7,8]. In addition, surgery is associated with direct costs as well as indirect costs related to work absence after surgery because the majority of patients require sick leave for a varying length of time depending on the degree of postoperative morbidity and the type of work [9]. The median time of work absence has been 4 weeks in several studies, with a proportion of patients having long-term work disability [9]. The economic impact of work absence following surgery for CTS can be substantial both for the patients and the society. Consequently avoiding sick leave would be an important advantage for nonsurgical treatment.

Although many alternatives to surgery have been proposed there is little evidence to support the efficacy of most of these treatments [10]. Steroid injection into or proximal to the carpal tunnel is widely practiced in the treatment of patients with idiopathic CTS particularly in the United States [11]. However, the evidence for its efficacy beyond one month has not been established in placebo-controlled trials. In a recent Cochrane review of local corticosteroid injection for CTS, the authors concluded that there was evidence supporting clinical improvement at one month compared to placebo but no significant improvement after 8 weeks compared to nonsteroidal anti-inflammatory drugs or wrist splint [12]. None of the studies reviewed involved a double-blind comparison with a follow-up of more than one month.

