### Outcome Measures

The CTS symptoms severity scale is a validated 11-item questionnaire that mainly inquires about severity, frequency and duration of night and daytime pain and numbness or tingling [14,15]. The CTS score ranges from 1 (no symptoms) to 5 (most severe symptoms). The *Quick*DASH is a validated 11-item questionnaire that mainly inquires about difficulties in performing daily activities, yielding a score from 0 (no disability) to 100 (worst possible disability) [18]. The SF-6D is a validated health utility measure that is used to compare cost-effectiveness of different treatments and the value ranges from -0.11 (worst health) to 1.0 (perfect health) [19]. All AEs are recorded during 24 weeks. Duration of sick leave for employed patients is recorded.

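### The 24-week comparison of injection safety with placebo includes adverse events from the week-12 surgery, and no comparison confined to the injection is stated

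*Protocol article*

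**What the plan says.** The Discussion sets the safety question and its period: "During the first 24 weeks the safety of steroid injection in the carpal tunnel will also be evaluated in comparison with placebo". Outcome Measures sets what is collected: "All AEs are recorded during 24 weeks". Statistical Analysis sets how it is reported: "The AEs will be reported in table form and stratified in 4 groups according to severity; statistical comparison will be done when appropriate". It adds one interim look for the medicines agency: "When at least 60 patients have completed the 24-week visit the frequency of SAEs and of AEs with persistent symptoms will be calculated".

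Surgery falls in the middle of this period. Under Follow-up, "At 12 weeks the patient who had chosen to have surgery is operated on as scheduled", and the Discussion says that "all patients are given the choice to have surgery at 12 weeks if their symptoms have not improved adequately". Table 2 schedules AE recording at baseline and at weeks 5, 10 and 24, so the only AE visit after the operation date is week 24.

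On what surgery brings with it, the Background names "surgery-related pain and hand weakness [6]. These are common problems and may last several months after surgery". It also lists wound infection, regional pain syndrome and nerve injury as less common complications.

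**The concern.** The stated question is whether the injection is safe compared with placebo. The stated window answers a different one, because from week 12 to week 24 some patients in every arm are recovering from an operation on the same hand. Pain, weakness and nerve symptoms after surgery can be hard to tell from harm done by an injection into the carpal tunnel.

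Two effects follow. First, surgical events add a background to every arm, so a true injection excess stands out less. Second, the rate of surgery is itself a primary endpoint. If the steroid lowers it, the placebo arm collects more surgical events, and the steroid looks safer because it is effective. A real excess of injection harm could then be understated or missed.

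The article sees the problem for efficacy. The primary symptom score is taken at week 10, before planned surgery, and the later symptom model carries surgery as a covariate. No counterpart is stated for safety.

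**Working it through.** **What can be reproduced.** The article gives no expected surgery rate, AE rate or post-operative complication rate, so there is no figure on this point to reproduce. Its one calculable design figure, 102 patients, concerns the symptom score and has no bearing here.

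**Timing, from the article.**
- AE window: weeks 0 to 24.
- Planned surgery: week 12, so 24 - 12 = 12 weeks, half of the window, follow the operation date.
- Table 2 allows 7 days either side of weeks 10 and 12. The latest 10-week visit is day 70 + 7 = 77 and the earliest planned operation is day 84 - 7 = 77. Within these windows, AEs recorded up to the 10-week visit precede planned surgery.

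**Illustration; every rate below is assumed.** Let i be the risk of an AE from the injection procedure, s the share operated on, and c the risk that an operated patient has a surgical AE. Taking the two sources as independent, the proportion with any AE by week 24 is

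P = 1 - (1 - i)(1 - s × c).

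Two special cases show the two effects (subscripts P placebo, S steroid):
- Equal surgery in both arms: difference = (i_S - i_P)(1 - s × c). The true excess shrinks by the factor 1 - s × c.
- No true injection excess: difference = -(1 - i) × c × (s_P - s_S). This is zero only if the surgery shares are equal or surgery causes no recorded AEs.

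Worked example with i = 10% in both arms, 80% of placebo and 40% of steroid patients operated on, and c = 50%:
- placebo: 1 - 0.90 × (1 - 0.40) = 46%
- steroid: 1 - 0.90 × (1 - 0.20) = 28%
- difference: -18 points, with no true difference.

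Steroid minus placebo, in percentage points:

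| Operated, placebo / steroid | c | No true excess (10% v 10%) | True excess of +10 (20% v 10%) |
|---|---|---|---|
| 60% / 60% | 5% | 0.0 | +9.7 |
| 60% / 60% | 20% | 0.0 | +8.8 |
| 60% / 60% | 50% | 0.0 | +7.0 |
| 70% / 50% | 5% | -0.9 | +8.85 |
| 70% / 50% | 20% | -3.6 | +5.4 |
| 70% / 50% | 50% | -9.0 | -1.5 |
| 80% / 40% | 5% | -1.8 | +8.0 |
| 80% / 40% | 20% | -7.2 | +2.0 |
| 80% / 40% | 50% | -18.0 | -10.0 |

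The dilution is not confined to counting patients. If events are counted instead, with equal 60% surgery and c = 20%, the expected numbers per patient are 0.20 + 0.12 = 0.32 and 0.10 + 0.12 = 0.22. The difference stays at 0.10, but the ratio falls from 2.0 to 0.32 / 0.22 = 1.45.

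**The case against.** **Silence is not an error.** An article may leave onset windows and attribution of AEs to the full protocol or analysis plan, and AEs recorded at weeks 5 and 10 can be tabulated by visit. This stands as far as it goes, and nothing in the article forbids such a table. But the article does more than omit detail. It names the window, the collection rule and the stratification, and together these do not isolate the question it names.

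**The 24-week comparison by randomised arm is valid.** This also stands. A reader might infer that the 24-week table is wrong; it is not. It is an intention-to-treat comparison of a policy: injection, then surgery if wanted. Sparing patients surgical morbidity is part of the case for nonsurgical treatment in the Background. The table simply does not measure the safety of the injection itself.

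**Direction and size are conditional.** A reader might infer that the plan will make the steroid look safer. The article does not support this as a fact. It requires fewer operations on steroid, which is what the trial tests, and post-operative pain or weakness being recorded as AEs, which the collection rule implies but does not spell out. The share of patients who will be operated on and the surgical technique are not stated either. Recruited patients are willing to have surgery and are placed on a waiting list, so a sizeable share is plausible, but that is an inference.

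**The interim count is not a comparison.** The plan says that "the frequency of SAEs and of AEs with persistent symptoms will be calculated", then reported to and discussed with the agency. A reader might infer that it is biased towards the steroid. No between-arm comparison is described; a pooled count with surgical events in it would overstate injection harm rather than hide it.

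**A split at the operation date has its own bias.** This stands. Surgery is chosen after randomisation on the strength of symptoms, so comparing arms before and after the operation date is not a randomised comparison. The fix respects this.

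**Conclusion.** The point holds in a conditional form. The stated window puts morbidity from elective surgery, which the article itself calls common, into the comparison from which injection safety is to be judged. Provided that surgical events are recorded as AEs, they obscure a true injection excess even with equal surgery rates. If the steroid also reduces surgery, they shift the comparison in its favour.

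The size cannot be derived from the article. Under the assumed rates (10% injection AE risk, 5% to 50% surgical AE risk, surgery shares from equal to 80% v 40%, independence), the difference with no true injection excess runs from 0 to -18 points. A true excess of +10 points would appear as anything from +9.7 to -10.0. With equal surgery rates and no injection harm, the shift is zero. The weakness lies in how the safety conclusion is to be drawn, not in the data collected, and it should be corrected before unblinded safety results are seen.

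**What to change.** - State that the conclusion on injection safety rests on a between-arm comparison of AEs with onset from injection to the 10-week visit. This precedes planned surgery, keeps the randomised comparison, and uses AEs already recorded at weeks 5 and 10.
- Keep the 24-week table of all AEs by randomised arm, labelled as the treatment-policy result. It also covers later events, including late effects of the injection.
- In that table and in the interim count of SAEs and persistent AEs, flag events with onset after the operation date. Present the flag as description only, with no test between arms, because surgery is a post-randomisation choice. Operation dates are needed anyway for the secondary endpoint of time to surgery; AE onset dates must be held as well.

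The cost is a few sentences and one more table, with no new visits or patients. The downside is that the injection-specific comparison covers about 10 weeks rather than 24. Injection effects that appear later are seen only in the table that also contains surgical events.
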